### Sample size {14}

To calculate the sample size (EPIDAT program) we proposed:

Expected sensibility: 78%Expected specificity: 87%Level of confidence: 95%

In order to evaluate ultrasound as a diagnostic test versus neurophysiological study in patients with a high clinical suspicion of suffering from CTS, expected values of sensitivity and specificity of the ultrasound test of 78% and 87% respectively, a maximum precision of 5% and a confidence level of 95% are considered, resulting in the need to evaluate a minimum of 264 patients with a positive result in the nerve conduction study as well as a minimum of 174 patients with a negative result, which means a total sample of 438 patients (Table 3). The number of positive and negative tests were known because the results were analysed by a secondary investigator. Therefore, the secondary investigator would indicate whether it was necessary to continue appointing patients for ultrasound scans until the total number of patients in both groups were obtained.

**Table 3 pone.0281221.t003:** Sample size.

Precision (%)	Sample Size		
	Positive test	Negative test	Total
5.000	264	174	**438**

The calculation was performed using the EPIDAT software, considering the parameters that underlie the calculation of the required sample size for conducting a diagnostic test evaluation study. The parameters requested by the software are based on sensitivity, specificity, and precision, which were obtained from previous studies.

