## Statistical methods

### Statistical methods for primary and secondary outcomes {20a}

After an initial exploration of the data, quantitative variables are expressed as means and standard deviations or medians and quartiles in case of asymmetric distributions, and qualitative variables as percentages.

The calculation of the measures of test accuracy of the ultrasound test as a diagnostic test for CTS: sensitivity, specificity, predictive values and likelihood ratios, are carried out considering the neurophysiological study as the reference test (gold standard).

Likewise, the reliability of the ultrasound is analyzed by calculating the degree of agreement between the diagnoses of the two tests using Cohen’s Kappa coefficient. The concordance of both tests with the established clinical severity is also studied.

The analysis of the quantitative variables did not present normality (Gaussian assumptions), therefore, for statistical inference, the Mann Whitney test (violations of Gaussianity) was used for independent quantitative variables. Shortly afterwards, a multivariate logistic regression model will be created to try to determine the best subset of them that predict CTS [20].

Finally, ROC curves will be performed to evaluate cut-off points for certain quantitative ultrasound parameters that discriminate well against CTS. In the ROC curves, the optimal cut-off point for greater sensitivity and specificity was determined by using the Youden index. In those ultrasound parameters where the ROC curve did not allow adequate discrimination, the median value of the data distribution was used.

In summary, the univariate analysis aims to identify which ultrasound parameters are related to the result of the CTS, thus providing elements of analysis to determine the cut-off points to be evaluated by means of ROC or medians, as well as the main variables to be considered in the multivariate model.

Data analysis is performed with SPSS 25.0 statistical software.

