In relation to the wrist-forearm index, the first to consider this parameter were Hobson-Webb and his team, who observed that in normal subjects the CSA in the wrist has been described as having the same value as that of the forearm and hypothesized that the ratio between the two could be a diagnostic alternative [29], on this basis, the wrist-forearm index should be 1:1. Both Hobson-Webb et al. [29] and Mhoon et al. [37] observed that values of 1.4 or higher have a high sensitivity (97–100%) to diagnose CTS and values below 1.4 a high sensitivity (99%) to rule it out, the low specificity (28%) limiting its use to screening only.

In our study, based on the approach of Hobson-Web et al. [29], we measured CSA at the tunnel entrance and 12 cm from the distal wrist crease. There are authors who have performed this index using different measurement references [38], so we will not, at the time, establish a comparison between their findings and those of our study. We took 1.4 as the cut-off point, as it is the most frequently considered cut-off point.

In relation to the Doppler tool, its usefulness lies in the fact that in healthy subjects intraneural blood flow has never been demonstrated, which seems to reflect a pathological condition. It has been observed that Doppler can detect increased intraneural or epineural vascular flow in patients with CTS, which seems to reinforce the diagnosis [39], and a correlation has been observed between intraneural flow and CTS severity [40].

When applying the doppler, the position of the wrist is very important, which could also influence blood flow.; the authors Vanderschueren et al. recommend keeping the wrist in a neutral position, avoiding mobilization of the fingers or provocation tests [41].

Another parameter studied over time has been the thickening of the flexor retinaculum in the proximal region of the carpal tunnel, the interest being based on the fact that continued inflammation and the consequent extraneural reactive fibrosis cause a greater thickness of this structure, considered in the pathological range above 1 mm [42]. In any case, in our opinion, like Pardal-Fernández [43], we consider it to be a parameter of low sensitivity, due to the small size of its dimensions and the consequent variability in measurements.

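### The ±5-point precision assumes an ultrasound-positive rule fixed in advance, but the plan takes cut-offs from the same patients by the Youden index

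*Protocol article*

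**What the plan says.** Protocol article, Sample size {14}, treats ultrasound as one yes/no test. The inputs are "Expected sensibility: 78" per cent, "Expected specificity: 87" per cent, and "a maximum precision of 5% and a confidence level of 95% are considered". The result is "a minimum of 264 patients with a positive result in the nerve conduction study" and "a minimum of 174 patients with a negative result", "which means a total sample of 438 patients".

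Statistical methods {20a} promises sensitivity, specificity, predictive values, likelihood ratios and Cohen's kappa against the neurophysiological test (NPT). All of these need a yes/no ultrasound diagnosis. The section does not say what makes an ultrasound positive overall. It then describes ROC curves for some of the quantitative parameters and states that "the optimal cut-off point for greater sensitivity and specificity was determined by using the Youden index". Where a ROC curve does not discriminate adequately, the sample median replaces the Youden value. A multivariable logistic model is also to pick the best-predicting subset of parameters in the same patients.

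The one cut-off taken from outside the study is in the Discussion, for the wrist-forearm index: "We took 1.4 as the cut-off point, as it is the most frequently considered cut-off point". For the retinaculum bulge, the Discussion leaves the best cut-off to be found.

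**The concern.** The precision formula describes a simple proportion. It is valid when the rule that labels each patient positive or negative does not depend on those patients' results. A Youden cut-off is chosen because it maximises sensitivity plus specificity in the sample, so part of its apparent performance is chance. The cut-off also varies from sample to sample, which an ordinary binomial interval ignores.

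The primary objective is the accuracy of ultrasound, and a secondary objective is to set reference values. If cut-offs and their accuracy come from one sample and are reported with ordinary binomial intervals, readers would receive slightly flattering figures with too little uncertainty attached, under a ±5% statement that was worked out for a different situation.

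**Working it through.** **1. Reproduce the plan's figure.** Inputs from Sample size {14}: sensitivity 0.78, specificity 0.87, d = 0.05, z = 1.96. Formula: n = z²·p(1−p)/d².
- Sensitivity: 1.96² × 0.78 × 0.22 / 0.05² = 263.7, so 264.
- Specificity: 1.96² × 0.87 × 0.13 / 0.05² = 173.8, so 174.
- Total: 264 + 174 = 438.

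The stated numbers reproduce exactly. The implied standard deviation of each estimate is 5/1.96 = 2.55 points. Simulating a fixed rule with these group sizes gives 1.96 × SD of 5.0 points for both measures, so ±5 is met in that case.

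**2. Let the Youden index choose the cut-off in the same sample.** The protocol gives no distributions, so a binormal parameter is assumed: NPT-negative N(0, 1) and NPT-positive N(2.21, 1.40²). These values put the true Youden optimum exactly at 78%/87%. There were 264 positives, 174 negatives and 10,000 simulated studies.

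| Quantity | Sensitivity | Specificity |
|---|---|---|
| True value at the best cut-off | 78.0% | 87.0% |
| Mean apparent value | 79.0% | 88.0% |
| Mean true value at the chosen cut-off | 77.8% | 86.5% |
| Optimism (apparent minus true at the chosen cut-off) | +1.2 | +1.5 |
| 1.96 × SD of the reported value | 8.8 | 8.3 |
| Coverage of the chosen cut-off's own true value | 91% | 88% |
| Coverage of the value at the best cut-off | 68% | 69% |

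Optimism in the sum is 1.2 + 1.5 = 2.7 points. Separate runs of the same model put the last row between 68% and 71%.

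**3. Vary the assumptions.**
- Equal-variance parameter: spread ±8.8/±9.0 points, optimism +1.2/+1.5.
- Coarsely rounded measurements: spread ±9.2/±8.8, optimism +0.6/+1.0.
- Best of five equally good parameters (assumed correlation 0.5; 3,000 studies): optimism +2.7/+3.0, and coverage of the chosen cut-off's own true values 79%/74%.

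On the variable list in Outcomes measures {12}, about four quantitative parameters are open to a Youden cut-off: cross-sectional area (CSA) at entrance, CSA at exit, the flattening ratio and the retinaculum bulge. The five-parameter run therefore shows the direction and rough size of the effect and is not a forecast.

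**The case against.** Several stronger readings are tempting, and the document does not support them.

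- **That the error is nearly doubled.** A reader might take ±8 to 9 points and 68 to 70% coverage as the error in the reported test's accuracy. Those figures measure distance from the best possible cut-off. Around the chosen cut-off's own true performance, the SD of the error is only about 2.5 points, no larger than the 2.55 assumed. Reported sensitivity and specificity correlate at about −0.70, and the SD of their sum is 3.4 points against 3.6 for a fixed rule. Most of the extra spread is the cut-off sliding along the ROC curve and trading one measure for the other. This part of the objection stands, so both sets of figures are needed.
- **That primary accuracy is certainly computed at Youden cut-offs.** No sentence says so. The ROC step could serve only the secondary objective on reference values. The inference rests on there being one sample and no other overall positivity rule.
- **That a useless parameter would gain several points.** The median rule in {20a} removes the Youden choice where discrimination is poor.
- **That two rules conflict for the wrist-forearm index.** The ROC step covers only some parameters, so the fixed 1.4 is compatible with it.
- **That every listed parameter is affected.** Doppler uptake and notches are presence-type findings, and the index has its fixed value.
- **That missing validation is itself the fault.** An article may leave that to a fuller document, and {20b}, whose heading gives subgroup analyses as its example, does not clearly exclude a bootstrap.

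What remains is a stated selection method that does not fit a stated precision. That is more than an omitted detail.

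**Conclusion.** The point holds and should be corrected, but it is moderate in size. The arithmetic behind 438 is right; the ±5 points it delivers do not carry over to cut-offs chosen in the same patients. For one parameter performing as the plan expects, the overstatement is about 1.2 points in sensitivity and 1.5 in specificity, well inside ±5. Nominal 95% intervals then perform as roughly 91% and 88% intervals for the cut-off actually reported. They do much worse, about 68 to 70%, if the figures are read as the accuracy at the optimal cut-off, which is how a proposed reference value is likely to be read. Reporting the best of several parameters or a selected model makes the optimism larger.

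These sizes rest on the assumed binormal parameter and, for the five-parameter case, on equal performance and a correlation of 0.5. The link from Youden cut-offs to the primary accuracy figures is inferred.

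**What to change.** 1. In {14}, restrict the ±5% statement to positivity rules fixed in advance. Examples are the wrist-forearm index at 1.4 and any CSA cut-off that the investigators fix from the literature before ultrasound and NPT data are merged. A fixed rule gives ±5 only if accuracy is near the values assumed. The Discussion reports a specificity of 28% for the index, and at that value 1.96 × √(0.28 × 0.72/174) = 6.7 points.
2. In {20a}, say which ultrasound-positive rule gives the primary sensitivity, specificity and kappa.
3. Label Youden- and median-derived cut-offs exploratory. Report their sensitivity, specificity and AUC with bootstrap optimism correction, and with intervals that repeat the cut-off and variable selection in every resample.
4. If the data have already been examined, make the bootstrap-corrected figures the headline, because a rule named now would not be prespecified. The past-tense remark in {20a} that the quantitative variables were not normally distributed suggests this may be so.

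Cost: wording changes and a short script, with no new patients. Reported accuracy will be slightly lower and its intervals wider.

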## Objectives {7}

**Primary**: To assess the accurancy of ultrasound in the diagnosis of CTS with respect to nerve conduction studies.

Secondary:

To determine the set of ultrasound parameters (ultrasound standards and reference values) that best predict the existence of CTS.To evaluate the relationship between the intensity or degree of involvement between ultrasound findings and nerve conduction studies.To propose a standardised protocol for the study of CTS by ultrasound.To perform a descriptive cost-effectiveness analysis between ultrasound and neurophysiological studies in the diagnosis of CTS.To detect and describe qualitative anatomical alterations and pathological findings that could predispose to the presence of CTS.

**Hypothesis**: Ultrasound is more accurate than neurophysiological studies in the diagnosis of CTS.

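### Univariate results choose the main variables for the logistic model, although the objective is a joint one and the sample can carry all the ultrasound parameters together

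*Protocol article*

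**What the plan says.** The first secondary objective (Objectives {7}) is "To determine the set of ultrasound parameters (ultrasound standards and reference values) that best predict the existence of CTS".

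Statistical methods for primary and secondary outcomes {20a} describes Mann-Whitney comparisons of the quantitative variables, then a multivariable logistic regression to find the best predictive subset, then ROC curves with Youden cut-offs for single parameters. Its closing summary gives the logic of the sequence: "the univariate analysis aims to identify which ultrasound parameters are related to the result of the CTS". From this follow the cut-off points, "as well as the main variables to be considered in the multivariate model".

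No p-value or other threshold for passing from the univariate step to the model is given, and no parameter is named as staying in regardless of its univariate result.

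Sample size {14} asks for "a minimum of 264 patients with a positive result in the nerve conduction study" and "a minimum of 174 patients with a negative result".

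**The concern.** Which set predicts best is a joint question. A univariate test asks whether a parameter differs between the groups when everything else is ignored. The two answers can differ when predictors are related, and here they are related by construction: under Outcomes measures {12} the wrist-forearm index has entrance cross-sectional area (CSA) as its numerator, and entrance CSA, exit CSA and the flattening (thinning) ratio all describe the same nerve.

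The protocol itself points to one parameter that could fall at the first step. The Discussion cites a study that measured flattening at the pisiform, hamate and lunate and found a group difference only at the hamate, and says that a meta-analysis agreed. Outcomes measures {12} takes the ratio at the pisiform. The Discussion also hopes to clarify the usefulness of this ratio. A univariate gate could remove it before its value in addition to CSA is examined.

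At stake is the composition of the recommended set, which also feeds the aim of proposing a standardised ultrasound protocol.

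**Working it through.** **1. The plan's own sample size.** Inputs from Sample size {14}: sensitivity 78%, specificity 87%, precision 5%, confidence 95%. Formula: n = 1.96² × p(1 − p) / 0.05².
- p = 0.78: 263.68, rounded up to 264.
- p = 0.87: 173.79, rounded up to 174.
- Total 438. The stated figures are reproduced exactly.

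**2. Number of candidates.** Study setting {9} lists entrance CSA, exit CSA, thinning ratio, wrist-forearm index, retinaculum bulge, power Doppler and masses: seven. Outcomes measures {12} lists the first six and notches, without masses: also seven. The union is eight. The article states no count.

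**3. Patients per parameter in the smaller class.** 174/8 = 21.75 and 174/7 = 24.9. At 10 patients per term the sample carries 174/10 = 17 terms; at 20 per term it carries 174/20 = 8.

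**4. Minimum size for a model with eight terms.** Outcome share 264/438 = 0.603, so the maximum Cox-Snell R² is 0.739. For an expected shrinkage of 0.90, n = 8 / [(0.90 − 1) × ln(1 − R²/0.90)], where R² is the Cox-Snell value (Nagelkerke value × 0.739).

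| Assumed Nagelkerke R² | Minimum n | Expected shrinkage at 438 |
|---|---|---|
| 0.15 | 609 | 0.84 |
| 0.20 | 446 | 0.89 |
| 0.30 | 283 | 0.93 |
| 0.40 | 201 | 0.95 |

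Estimating the overall outcome share to within 5 points needs 368. The protocol's expected 78% and 87%, treated as one binary predictor in 264 and 174 patients, give a likelihood-ratio statistic of 193.7. Cox-Snell R² is then 1 − exp(−193.7/438) = 0.357, Nagelkerke R² is 0.357/0.739 = 0.48, and expected shrinkage is 1 − 8/193.7 = 0.96. At the accuracy the protocol expects, 438 is enough for eight single terms.

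**5. How often a screen loses a parameter.** Two correlated predictors, 264 and 174 patients, Mann-Whitney screen at p < 0.05, 400 runs per row. The first predictor has a log-odds of 1 per SD. The threshold, correlations and effects are all assumptions.

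| Correlation | Second effect (log-odds per SD) | Dropped by screen | Significant in joint model |
|---|---|---|---|
| 0.3 | −0.3 | 94% | 79% |
| 0.5 | −0.5 | 95% | 99% |
| 0.6 | −0.5 | 86% | 97% |
| 0.6 | −0.6 | 94% | 99% |
| 0.7 | −0.7 | 97% | 100% |
| 0.6 | +0.4 | 0% | 78% |

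**6. Cost in discrimination.** A second simulation (300 trials, eight correlated parameters, one of them masked when taken alone, p < 0.05 screen, assumed effects) gave a mean true AUC of 0.803 for the full model and 0.795 after screening, a difference of 0.008. The masked parameter survived the screen in 9% of trials.

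**The case against.** The strongest reply has four parts.

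- **The text sets no gate.** It speaks of main variables to be considered and leaves the final subset to the logistic model. This stands in part. Pre-selection is the natural reading, but strict exclusion at a fixed p-value is not stated.
- **Masking is unlikely here.** The Discussion describes markers that move in the same direction: CSA rises, Doppler flow appears, and a high index, a high flattening ratio and a bulging retinaculum all point to CTS. In the same-direction row of the table nothing was dropped. Entrance CSA and the index in particular are unlikely to look null alone, since the Discussion cites 97–100% sensitivity for an index of 1.4 or more. This stands, and it limits the size of the concern. It does not cover the flattening ratio at the pisiform, although the cited evidence shows only that this ratio is weak alone, not that it adds to the others.
- **Masses may not be meant for the model.** Anatomical alterations have their own descriptive objective. This is fair, and the count of seven allows for it.
- **Validation and selection details belong in an analysis plan that is not shown.** Agreed: their absence from a condensed article is not part of this point. The pre-selection step is stated in the article.

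A reader might infer that screening makes reported performance more optimistic than fitting everything. The simulation does not support this: apparent minus true AUC was 0.818 − 0.803 = 0.015 for the full model and 0.807 − 0.795 = 0.012 after screening. A reader might also infer that the parameters enter the model dichotomised at their Youden cut-offs. The section names cut-offs and model variables as separate products and does not say this. Nor does it plan an AUC for the multivariable model.

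**Conclusion.** The point holds as a weakness in how one secondary objective is analysed. The stated univariate step is poorly matched to a question about a joint set, and the sample does not require it: about 22 to 25 patients with a negative neurophysiological test are available per listed ultrasound parameter.

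The size is uncertain and may be small. A parameter is lost often (86–97% of runs in the opposing-effect scenarios) only if related parameters mask its marginal effect. With effects in the same direction the loss was nil. The expected cost in AUC is about 0.008. What matters is the chance of reporting the wrong set.

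The conclusion that the sample suffices assumes one linear or binary term per ultrasound parameter, all 438 patients, and a model that is not weak. At a Nagelkerke R² of about 0.20 or below, or with demographic, questionnaire or non-linear terms added, the margin shrinks or disappears. Sensitivity, specificity and kappa do not depend on this model.

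**What to change.** In Statistical methods {20a}, list the ultrasound parameters in advance and enter them together in one logistic model, with the measured ones kept continuous. Masses may stay descriptive if they prove too rare to model. Say that the Mann-Whitney tests describe the groups and do not decide entry to the model.

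If a smaller set is wanted, reduce that full model by backward elimination or LASSO, repeat the whole selection in bootstrap samples, and report how often each parameter is selected. If an AUC for the model is reported, give its optimism-corrected value.

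The cost is a few sentences of text and a bootstrap run, with no new patients or measurements. Coefficients of closely related parameters, such as entrance CSA and the index, will have wider intervals in the joint model, which should be said when they are interpreted.

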### Methods for additional analyses (e.g. subgroup analyses) {20b}

Not applicable, no additional analysis will be performed.

### Methods in analysis to handle protocol non-adherence and any statistical methods to handle missing data {20c}

The main analysis will be the concordance between the results of electroneurography and ultrasound in the diagnosis of CTS. Different parameters will be considered and in case of missing values these will be imputed by multiple imputation, selecting some of the methods that best suits the data set, the maximum interaction method, monotonic method, linear regression, predictive mean matching (PMC) among others.

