#### Plans to promote participant retention and complete follow-up {18b}

Not applicable. The data collection is a one-time ultrasound and the are no further revisions or assessments scheduled after. Initially, patients undergo neurophysiological testing. Therefore, the Neurophysiology Service refers the patients 1 to 3 months after the neurophysiological test has been performed. Subsequently, patients are contacted by the principal investigator to schedule the ultrasound scan. If the patient attends the ultrasound, he/she is included in the sample. Otherwise, the patient is not included.

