The flattening ratio is a ratio between the transverse and anteroposterior diameters in the intracarpal region, described within the tunnel. It is a well-regarded parameter [44] and ratios above 3.5–4 are considered pathological. At the mid-distal level, in the ulnar nerve, some authors have shown that the trapped nerve presents a morphological deformation of its floor, in such a way that it outlines the contour or ridge of the tendons it contacts, showing a deformity similar to a “triangular” [45]. In turn, the authors Lee et al. analyzed different ultrasound variables including the flattening index, but at different levels of the tunnel: at the pisiform, hamate and lunate. Statistically significant differences were only obtained between both groups in the measurement made at the level of the hamate (cut-off point 3. 2+/-0.4 P<0.05) [46]. These same results were found by Tai et al. in a meta-analysis carried out in 2012 [47]. In any case, some authors did not find cost-effectiveness in this parameter [48]. We have included it in our parameters and hope to clarify its usefulness.

The flexor retinaculum may bulge as a result of increased intracarpal pressure. The buckling of the flexor retinaculum, in most CTSs, is usually not important considering the low elasticity of this structure, especially if it is also fibrosed. In any case and taking into account that the image at this point is not usually good, these findings are not very conclusive due to their low reproducibility. We have included this parameter in our measurements, finding it useful based on the literature analyzed and hoping to clarify the best cut-off point.

The mobility patterns of the nerve in patients with CTS have also been analyzed. Chen et al. [10] also included in their protocol a "stress test" when flexing the first finger and when flexing the rest of the fingers (changes in the diameter of the nerve without measuring) as well as the lumbrical test (to determine whether they invade the tunnel when performing a full grip). We found the performance and assessment of these tests to be highly dependent on the experience of the examiner, which is why we have dispensed with dynamic tests in the development of our protocol.

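### The missing-data rule imputes every missing value without separating ultrasound readings that could not be obtained from values that were not recorded, so accuracy for a parameter may be overstated.

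*Protocol article*

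**What the plan says.** Section {20c} of the protocol article first names the analysis: "The main analysis will be the concordance between the results of electroneurography and ultrasound in the diagnosis of CTS". It then states that "in case of missing values these will be imputed by multiple imputation", and leaves the technique open: "selecting some of the methods that best suits the data set". No type of variable is exempt. The rule therefore reaches the ultrasound readings behind the accuracy measures, kappa, ROC cut-offs and logistic model of section {20a}.

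Section {18b} fixes who is in the sample: "If the patient attends the ultrasound, he/she is included in the sample". For everyone else, "Otherwise, the patient is not included". There is one visit only: "The data collection is a one-time ultrasound".

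On image quality, the Discussion says of the flexor retinaculum bulge: "taking into account that the image at this point is not usually good". It gives no rate of failed readings for this or any other parameter.

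**The concern.** In a study of diagnostic accuracy, a reading that was attempted and could not be obtained is an outcome of the test under study. It does not stand for a hidden number that better record keeping would have supplied. If it is imputed, a patient for whom ultrasound gave no reading is assigned one, and the test is credited with whatever accuracy the imputation model carries over from the readable scans.

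The sampling rule makes this relevant. Non-attendance and dropout, the usual causes of missing data, cannot produce a missing ultrasound value here. Unobtained readings and recording gaps remain, and they need different handling.

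The secondary objectives include finding the best set of parameters with reference values and proposing a standard scanning protocol. How often each parameter cannot be read bears directly on both, and imputation without a separate count would hide it.

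**Working it through.** **Inputs.** From the Sample size section {14}: expected sensitivity 78%, specificity 87%, precision 5 points, confidence 95%, 264 NPT-positive and 174 NPT-negative patients. The document gives no share *f* of unobtainable readings, so *f* is assumed and varied. The 78% and 87% are the plan's figures for ultrasound as a whole. Applying them to a single parameter is a second assumption.

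**The plan's own figure.** n = 1.96² × p(1 − p) / 0.05².
- Sensitivity: p = 0.78 gives 263.68, rounded up to 264.
- Specificity: p = 0.87 gives 173.79, rounded up to 174.

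The total of 438 reproduces, so 5 points is a fair yardstick.

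**Accuracy by handling of unobtainable readings.**
- Imputed at random within NPT group: expected values stay at 78% and 87% for any *f*.
- Counted as errors: 0.78(1 − f) and 0.87(1 − f).
- Counted as test-negative: 0.78(1 − f) and 0.87(1 − f) + f.

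| Assumed f | Imputed (Se / Sp) | Counted as errors | Counted as test-negative |
|---|---|---|---|
| 1% | 78.0 / 87.0 | 77.2 / 86.1 | 77.2 / 87.1 |
| 2% | 78.0 / 87.0 | 76.4 / 85.3 | 76.4 / 87.3 |
| 5% | 78.0 / 87.0 | 74.1 / 82.7 | 74.1 / 87.7 |
| 10% | 78.0 / 87.0 | 70.2 / 78.3 | 70.2 / 88.3 |

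With failures as errors, the gap at 2% is 0.02 × 78 = 1.6 points for sensitivity and 0.02 × 87 = 1.7 points for specificity. It reaches 5 points at f = 0.05/0.78 = 6.4% (about 17 of 264 patients) for sensitivity, and at f = 0.05/0.87 = 5.7% (10 of 174) for specificity.

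**If the imputation model omits the NPT result.** Take the crudest case, where imputed results are drawn at the overall positive rate.
- Positive rate: 264/438 = 0.603, so 0.603 × 0.78 + 0.397 × 0.13 = 0.522.
- Sensitivity at f = 10%: 0.9 × 0.78 + 0.1 × 0.522 = 75.4%.
- Specificity at f = 10%: 0.9 × 0.87 + 0.1 × 0.478 = 83.1%.

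Both still exceed the 70.2% and 78.3% obtained with failures as errors. This case ignores the patient's other ultrasound readings, which a real model would probably use, so it is an extreme.

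**Simulation** (normal model, 264/174 patients, 400 replicates, 10 imputations within NPT group).
- Readings missing at random, f = 5%: imputation gave 78.3% and 87.1%, the same as the full data.
- Missing readings in NPT-positive patients assumed to lie 1 SD closer to normal: imputed sensitivity was 78.2% against a full-data value of 76.4% at f = 5%, and 78.0% against 74.2% at f = 10%. Specificity was not inflated.

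**The case against.** The document does not say why values would be missing. A reader might infer that missing ultrasound values are mostly failed readings and that accuracy is therefore overstated. The text does not support that much. Section {18b} rules out non-attendance and dropout but does not show how the rest divides. Section {19} describes data entry in batches of 50 with a later check, so recording gaps are possible, and for gaps that are missing at random imputation is sound. The rule also covers covariates and questionnaire items, where nobody would object to it.

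The only remark on poor images concerns the retinaculum bulge, and it leads to a statement about low reproducibility, which describes noisy readings more than absent ones. Nor does one missing parameter make a whole scan non-diagnostic: a patient without a bulge reading may still have both cross-sectional areas, the wrist-forearm index and the Doppler result.

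The size depends on how failures are counted. Counting them as errors in both groups is the harshest convention. Counted as test-negative, only sensitivity is overstated, and imputation slightly understates specificity. Counted as test-positive, the pattern reverses: at f = 10%, sensitivity would be 0.702 + 0.10 = 80.2% and specificity 78.3%.

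Finally, the coding of inconclusive results is often left to an analysis plan, and none is shown. All of this stands and makes the point conditional. It does not remove it, because section {20c} goes beyond leaving the matter open: it states a rule without exception, and that rule covers failed readings.

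**Conclusion.** The point holds in conditional form. The stated rule treats unobtained readings and unrecorded values alike, and for unobtained readings imputation credits ultrasound with results it did not give. Accuracy for the parameter concerned, sensitivity at least when failures count as errors or as test-negative, may then be overstated.

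With failures counted as errors, the effect is under 2 points at failure rates of 2% or less and exceeds the planned 5-point precision only above about 6%. These rates are assumptions, and the calculation borrows the plan's overall 78% and 87% for a single parameter. If few readings fail, or if the gaps are recording omissions missing at random, little or nothing is lost. An 8-point shift in sensitivity (78.0% to 70.2%) needs an assumed 10% failure rate and should not be read as an expected effect.

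**What to change.** In section {20c}:

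- Restrict multiple imputation to values not recorded: covariates, questionnaire items and recording gaps.
- Give ultrasound readings that were attempted but not obtained their own code, non-diagnostic, and do not impute them.
- Report the number of non-diagnostic readings by parameter and by NPT result.
- For each parameter, give sensitivity and specificity with non-diagnostic readings kept in the denominator (counted as errors), next to the values in readable scans.
- Treat the overall ultrasound diagnosis as non-diagnostic only where the missing parameter prevents a diagnosis.

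The cost is one extra code in the data sheet and one extra table. The stated accuracy may become slightly less favourable. No additional patients are needed.
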